| Statistical Analysis:                   | 
As this study is a feasibility study, this study is not powered to achieve statistical significance. Rather we are aiming to understand if we can
 
 
a) recruit men and women of South Asian origin to an intensive weight management intervention
 
b) if the intervention is acceptable to the South Asian population
 
c) if individuals of South Asian origin can lose weight and achieve diabetes remission with the intervention
 
d) how the programme can be improved for use in a larger randomised controlled trial
 
e) define the mechanisms behind Type 2 diabetes remission in the South Asian population
 
                                                                                                                                                                                                                                                                                                                                                                                                                                                                                                                                                                               |

|  |  |
|--|--|
|  |  |
|--|--|

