| Primary Objective:   | To determine the feasibility and acceptability of an intensive weight management programme in South Asian patients to achieve remission of diabetes at 3 months.                                                                                                                                                                                                                                                                                                                                                                                                                                                                                                                                                                                                                                                                                                                                                                                                                                                                                                                                                                                                                                                                                                                                                                                                                                                                                                                                                                                                                                                                                                                                                                                                                                                   |

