| Primary Endpoint:    | Percentage achieving $\geq 15$ kg weight loss, and/or HbA1c $< 48$ mmol/l, off treatment, at end Total Diet Replacement stage to inform larger randomised controlled trial                                                                                                                                                                                                                                                                                                                                                                                                                                                                                                                                                                                                                                                                                                                                                                                                                                                                                                                                                                                                                                                                                                                                                                                                                                                                                                                                                                                                                                                                                                                                                                                                                                         |

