### **3.2 Inclusion criteria**

- Written informed consent
- Men and women aged 18-65 years
- South Asian ethnicities
- Body mass index (BMI)  $>25 \text{ kg/m}^2$  and  $<45 \text{ kg/m}^2$
- T2DM of duration 0-4 years (diagnosis based on a recorded diagnostic-level test: HbA1c and/or blood glucose)
- HbA1c  $\geq 48 \text{ mmol/mol}$  and/or fasting plasma glucose  $\geq 7 \text{ mmol/l}$  within last 12 months

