## **4 Trial procedures**

Patients will all be seen at the Glasgow Clinical Research Facility for all appointments.

Patients randomised to control will be advised to continue with usual care for 3 months before coming back to receive the intervention. They will be asked not to aim to lose any weight during the initial control period, but rather to wait until they commence the intervention part of the study. An appointment will be given to the patient for 3-months' time, and they will commence the intervention at that point.

Patients randomised to intervention will commence Counterweight Plus, which includes a TDR phase followed by structured food reintroduction. This will be delivered by research Dietitians experienced in programme delivery.

**TDR phase (0 to 12-20wks):** A commercial micronutrient-replete 825-853kcal/d LELD will be provided (Cambridge Weight Plan) to replace normal foods, with ample fluids, for 12-20 weeks. Oral hypoglycaemic agents (OHA), antihypertensive and diuretic drugs will be withdrawn on commencement of TDR, and reintroduced (according to guidelines) if diabetes or hypertension returns. Aspirin will be continued in patients prescribed this because of a previous MI (prior to the previous 6 months), but will be discontinued in patients who are prescribed it purely because they have T2D. Beta-blockers will be continued in patients prescribed these for the management of angina. A soluble fibre supplement (Fybogel 2x3.5g/day) will be prescribed to avoid constipation.

Participants will return for review one week after commencement on the TDR and at 2 weekly intervals thereafter till week 12-20 (total of 7-13 appointments) and the commencement of the food reintroduction stage.

To allow some flexibility for patients whose commitments, or practical limitations vary, the TDR phase will be permitted to continue up to 20 weeks if they fail to lose >15kg by week 12. Any patient whose BMI falls below 22 kg/m^2, before week 12 will be moved forward to 'food reintroduction and weight maintenance'. Reasons for moving to food reintroduction prior to week 12 will be recorded.

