#### **4.2 Study Outcome Measures**

The main study outcome measures are as follows:

- Numbers recruited into the intervention
- Programme retention
- The acceptability of the intervention to people of South Asian origin
- Weight loss achieved (kg, %), and diabetes remission. Remission is defined as a return of HbA1c to <48mmol/mol (<6.5%) that occurs spontaneously or following an intervention, and off all usual glucose-lowering pharmacotherapy for at least 3 months
- Define the mechanisms behind type 2 diabetes remission in the South Asian population

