## **6.1 Sample size**

We aim to recruit 25 participants to the study. This figure has been chosen as this will give us enough information to assess the feasibility and acceptability of the programme to this population. We anticipate a failure to complete rate of about 25% (this may be greater at specific timepoints due to the COVID-19 pandemic). With 20 participants in a randomized comparison, the study can estimate the change in weight with a margin of error of 2.8kg assuming a standard deviation weight change over 3 months of 6kg. e.g., for an average observed weight change of 8kg (SD 6) we can estimate with 95% confidence that in the population the true weight change would lie between 5.1 and 10.7kg.

The proportion achieving remission in the combined intervention and delayed intervention groups (n=20) will be compared to the proportion achieving diabetes remission in the external DIADEM-1 trial control group (Taheri et al, Lancet Diabetes and Endocrinol, 2020) (12%; 95%CI 5%, 21%). Therefore assuming 12% remission in a usual care group (based on DIADEM), using a one sample proportion test, with 20 participants there will be 83% power to detect a significant difference if 30% of participants (n=6) or more achieve remission.

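### The primary endpoint counts a 15 kg loss without remission and can credit participants already below 48 mmol/mol at baseline, so it is not the remission rate compared with 12%

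*Protocol*

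**What the plan says.** - **Primary endpoint (Study Synopsis).** The percentage with at least 15 "kg weight loss, and/or HbA1c" below 48, with the unit printed as mmol/l, "off treatment, at end Total Diet Replacement stage to inform larger randomised controlled trial".
- **Primary objective (Study Synopsis).** Feasibility and acceptability of the programme "to achieve remission of diabetes at 3 months".
- **Remission (section 4.2).** The definition begins "Remission is defined as a return of HbA1c to <48mmol/mol (<6.5" per cent) and adds the condition "off all usual glucose-lowering pharmacotherapy for at least 3 months". The unit here is mmol/mol.
- **Hypothesis test (section 6.1).** "The proportion achieving remission in the combined intervention and delayed intervention groups (n=20") is compared with 12% from an external control group by a one-sample proportion test. The example is 30%, or 6 of 20. The same section also gives the precision of the mean weight change.
- **Entry (section 3.2).** HbA1c of 48 mmol/mol or more and/or fasting glucose of 7 mmol/l or more, "within last 12 months". BMI must be above 25 and below 45.
- **Baseline visit (section 4.1).** The HbA1c sample and randomisation fall in the same appointment, and no HbA1c threshold is attached to that sample.
- **TDR rules (section 4).** "Any patient whose BMI falls below 22" before week 12 is moved forward to food reintroduction. TDR may run to week 20 if more than 15 kg has not been lost by week 12.

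**The concern.** Joined by and/or, the endpoint is a union, and three things follow.

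1. The headline percentage mixes a weight target with remission. It is meant to inform a larger trial, and a mixed figure cannot supply that trial's remission rate. It is also not the quantity that section 6.1 compares with 12%.
2. The HbA1c limb asks only for a value below 48 at the end of TDR. It does not ask that the value was 48 or above beforehand. A person admitted on an old HbA1c, or on fasting glucose alone, who is untreated and already below 48 can count as a success with no change.
3. A fixed 15 kg is a much larger share of body weight for a person who enters near BMI 25, and the BMI 22 rule can end TDR before 15 kg is lost. The limb that produces success then differs with entry BMI.

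**Working it through.** **Setting the definitions side by side**

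| Participant at end of TDR, off drugs | Primary endpoint | Remission (4.2) |
|---|---|---|
| Lost 15 kg, HbA1c 48 or more | success | no |
| Untreated and below 48 at baseline, still below 48 | success | no return to below 48 has occurred |
| Previously treated, now below 48, at 12 weeks | success | depends on the 3-month condition |

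On the last row: oral agents stop when TDR starts (section 4; listed at Appointment 1, week 0+1, in section 4.1). At the end of a 12-week TDR a treated participant has been off drugs for about 11 to 12 weeks, at or just short of 3 months.

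**Can someone below 48 enter?** Yes. Section 3.2 allows fasting glucose alone, or an HbA1c up to 12 months old. The exclusion for losing more than 5 kg (section 3.3) looks back 6 months, so it does not close a 12-month window.

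**Effect on the 6/20 threshold**

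Inputs from section 6.1: n = 20, reference rate 12%, example result 6/20. With exact binomial tails:

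- At 12% with nobody credited in advance: P(X ≥ 6 | 20, 0.12) = 0.026.
- At 30%: P(X ≥ 6 | 20, 0.30) = 0.58. The printed power is 83%, which this does not reproduce. That is a separate matter, and nothing below uses it.

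Let k participants be counted as successes because they were already below 48 untreated, and let the other 20 − k remit at 12%. The chance of 6 or more is P(X ≥ 6 − k | 20 − k, 0.12). The documents give no k, so a range is shown.

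| k (assumed) | Expected percentage, (k + 0.12(20 − k))/20 | Chance of 6/20 or more |
|---|---|---|
| 0 | 12.0% | 2.6% |
| 1 | 16.4% | 6.9% |
| 2 | 20.8% | 16% |
| 3 | 25.2% | 33% |

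**The weight limb**

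The loss that takes BMI 25 to 22 is 3h² kg. The entry BMI that leaves BMI at 22 or above after losing 15 kg is 22 + 15/h². Heights are illustrative.

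| Height h | 3h² | 22 + 15/h² | 15 kg as share of weight at BMI 25 |
|---|---|---|---|
| 1.60 m | 7.7 kg | 27.9 | 15/64.0 = 23% |
| 1.65 m | 8.2 kg | 27.5 | 15/68.1 = 22% |
| 1.70 m | 8.7 kg | 27.2 | 15/72.2 = 21% |

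The BMI 22 rule is worded only for the time before week 12. Suppose weight falls at a constant pace and 15 kg is reached at week 20. The loss by week 12 is then 15 × 12/20 = 9 kg, and the entry BMI needed to be at 22 or above at week 12 is 22 + 9/h²: 25.5 at 1.60 m and 25.1 at 1.70 m. Between this bound and 22 + 15/h², whether 15 kg can be reached depends on pace.

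**The case against.** The best defence is that this is a feasibility study. It disclaims power, and it states its focus as acceptability together with weight change and remission (Study Synopsis, Rationale; section 1.3). A weight limb fits that aim, and section 6.1 itself treats weight-change precision before it turns to remission. This stands: a weight outcome belongs in the study, and it would be wrong to say that section 6.1 concerns remission alone. It does not rescue the union, because the only test and the only external benchmark are for remission.

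Four stronger readings are tempting but unsupported:

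- **That an untreated entrant below 48 meets the endpoint on day 0.** The endpoint is assessed at the end of TDR. Such a person meets the threshold at baseline and must still meet it then.
- **That 15 kg is out of reach for lean entrants.** The BMI 22 rule is stated only before week 12, so this is strict only for the leanest, shorter entrants and for those who lose fast enough to cross 22 early. All of them can still succeed through HbA1c.
- **That the BMI 22 rule and the extension to week 20 contradict each other.** They can be read in sequence: someone moved forward before week 12 is no longer on TDR when the extension is considered.
- **That 16% is the false-positive rate of the planned test.** It rests on an assumed count. The test is also on remission, and under section 4.2 someone already below 48 arguably has no return to make. The figures apply only if such people are counted.

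**Conclusion.** The concern holds in a limited form. On the text alone, the primary endpoint can be met without remission, and participants who were untreated and below 48 at baseline can be credited. It is therefore not the rate that section 6.1 compares with 12%.

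Each participant credited in this way adds 5 percentage points at n = 20. With 1 to 3 of them, and the others remitting at 12%, the chance of 6/20 or more goes from 2.6% to between 6.9% and 33%. The number of such people is an assumption; that they can enter follows from section 3.2. The weight limb is harder for leaner entrants, roughly those below BMI 27.2 to 27.9 at 1.60 to 1.70 m, to a degree that depends on pace. The HbA1c limb remains open to them, so the composite means different things across the entry range.

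This is worth correcting before analysis, but it does not undermine the feasibility aims.

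**What to change.** 1. Make remission the primary clinical endpoint and the quantity compared with 12%: HbA1c below 48 mmol/mol (correcting the printed mmol/l), off glucose-lowering drugs.
2. Reconcile that endpoint with the requirement in section 4.2 of at least 3 months off drugs, since assessment after a 12-week TDR falls at about that limit. The synopsis, section 4.2 and section 6.1 should carry one definition.
3. Keep all participants in the main count. Also give the remission rate among those who had HbA1c of 48 mmol/mol or more, or took a glucose-lowering drug, at the last measurement before starting TDR. For the delayed arm this is the sample at the end of the control period (section 4.1; Appendix A, footnote c). List the others separately.
4. Confirm that drug use is recorded at that point. Neither the baseline visit in section 4.1 nor Appendix A lists it.
5. Report weight loss separately in kg and %, as section 4.2 already provides, with any responder cut expressed as a percentage of baseline weight.

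The cost is wording and one extra tabulation. The HbA1c samples are already scheduled; drug use may need one added field. The headline percentage will be lower than under the union, and the restricted count will have a slightly smaller denominator.

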|                             | 
At baseline and again after weight loss has been completed and weight stabilized (16-20 weeks), all participants will complete questionnaires on Quality of Life and have blood samples and anthropometric data collected. A questionnaire exploring participant's weight loss expectations and current diet will be administered at baseline.
 
Treatment acceptability will be assessed by questionnaire at the end of the study period
 
Intervention arm, consenting patients will undertake Counterweight-Plus, delivered by a research dietitian. Any existing anti-diabetic, anti-obesity and antihypertensive medications will be withdrawn at the start of 825-853kcal/day 'Total Diet Replacement' liquid diet phase. If necessary they will be reintroduced using standardised protocols according to blood glucose and BP increases. All other management of type 2 diabetes will continue as per clinical guidelines.
 
A questionnaire to quantify psychological process measures (motivation, self-efficacy, resources, self-regulation, habit, satisfaction with outcomes, diet/behaviour, goal conflict, goal facilitation, social support and environmental support) will be completed by participants at each intervention visit
 
An MRI scan will be performed at baseline and repeated after weight loss.
 
Participants will be invited to undergo additional measurements of Metabolic Rate (resting and during physical activity) and Body Composition. These tests will be optional
 
Control arm, patients will continue to be treated according to clinical guidelines.
 |

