#### **Appt 11 (Week 0+19, Final Appointment )**

- Venepuncture for HbA1c, urea and electrolytes, glucose, insulin, liver function tests, lipids.
- Measurement of weight & blood pressure
- Measurement of waist and hip circumference
- Psychological Process Questionnaire
- EQ-5D
- Process evaluation questionnaire
- MR, appetite hormone and Body Composition measurements if participant has consented to these

Final MR scanning will be undertaken at the point of maximal weight loss which will be either at the end of the TDR phase or end of food reintroduction

On completion of the study participants will be given advice, and written information, on maintaining weight loss, which will include goal setting, self-monitoring, physical activity, relapse prevention if weight tends to rise again, and education on food labelling and eating out. Participants will then be returned to the care of their GP, who will be informed.

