## **6. STATISTICS AND DATA ANALYSIS**

The main objective of the study is to investigate if Counterweight Plus is acceptable to individuals of South Asian origins. This study is not powered to achieve a primary outcome, rather to investigate if it is possible to recruit, retain and achieve remission from diabetes in the South Asian population. Data will be collected on paper-based forms and entered into a secure SPSS file for analysis. Drug intolerance, diet intolerance or poor-compliance will be recorded. Trial documentation and data will be retained for at least 5 years.

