## **7.0 STUDY CLOSURE / DEFINITION OF END OF STUDY**

The trial will last for 13 months in total. All participants will have completed 6 months follow-up by the end of the first year. This will give 6months to recruit all participants to the study.

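### Acceptability, the main objective, is asked about only at the final visit and no exit questionnaire is described, so rated acceptability is likely to be overstated

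*Protocol*

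**What the plan says.** Section 6 states: "The main objective of the study is to investigate if Counterweight Plus is acceptable to individuals of South Asian origins". The synopsis (Methodology) fixes when this is measured: "Treatment acceptability will be assessed by questionnaire at the end of the study period".

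In the visit list of section 4.1, the item "Process evaluation questionnaire" stands under one visit only, headed "Appt 11 (Week 0+19, Final Appointment". I take this to be the acceptability questionnaire, since no other visit lists a candidate. Appendix A has rows for the EQ-5D, the expectation questionnaire and the psychological process questionnaire, but none for this one.

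Section 6.1 says "We aim to recruit 25 participants to the study" and "We anticipate a failure to complete rate of about 25" per cent, and adds that the rate may be higher at some timepoints because of the pandemic. For people who withdraw, section 3.5 provides routine clinic or GP data, best available weights, diabetes status at the end, and a note of intolerance or poor compliance. It mentions no exit form or interview.

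Controls wait 3 months and then receive the programme. The synopsis gives one reason for this as adding to the number who can report on acceptability. On duration, section 7.0 says "The trial will last for 13 months in total", with 6 months for recruitment. The synopsis gives 1 year for the study and 6 months for treatment.

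**The concern.** Disliking a liquid diet that lasts 12 to 20 weeks is an obvious reason to leave it. A questionnaire given only at the last visit reaches those who stayed, so whether a person is asked probably depends on the answer they would give. Even completers are asked about TDR only after food reintroduction.

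Two results are at stake. One is the figure for the main objective, which is meant to inform a larger trial. The other is the third research question in section 2, on what participants like, dislike or would change. Those who gave up are well placed to answer it, and views not collected when they leave may not be recoverable later.

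The delayed arm raises a second, smaller matter. If the study closes when section 7.0 says, some late-randomised controls may not reach Appt 11, although they are treated partly to supply acceptability data.

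**Working it through.** **1. How many are not asked.** Inputs: 25 recruited and about 25% not completing (section 6.1).

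- Completers: 25 × (1 − 0.25) = 18.75, about 19. Non-completers: about 6.
- The plan's own analysed number is 20 ("With 20 participants in a randomized comparison"). That is a 20% loss (5/25), within two people of 18.75, so the figures agree roughly.

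**2. Size of the overstatement.** Let *d* be the share not asked, *a* the proportion of completers who find the programme acceptable, and *b* the same proportion among non-completers.

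- Reported figure: *a*
- Figure over everyone: (1 − *d*)*a* + *d b*
- Overstatement: *d*(*a* − *b*), with *d* = 6/25 = 0.24

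The protocol gives neither *a* nor *b*, so both are assumed and shown over a range:

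| *a* (completers) | *b* = 0% | *b* = 25% | *b* = 50% | *b* = *a* |
|---|---|---|---|---|
| 70% | 16.8 points | 10.8 | 4.8 | 0 |
| 80% | 19.2 | 13.2 | 7.2 | 0 |
| 90% | 21.6 | 15.6 | 9.6 | 0 |
| 100% | 24.0 | 18.0 | 12.0 | 0 |

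For example, with *a* = 80% and *b* = 0% the figure over all 25 is 0.76 × 80% = 60.8%, against 80% reported. At the extreme, 19/19 = 100% would be reported against 19/25 = 76%. With the plan's 20 completers the maximum is 5/25 = 20 points.

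**3. Timeline for controls.** Inputs: 6 months of recruitment (section 7.0), a 3-month control period (section 4), Appt 11 at week 19 (section 4.1), TDR of 12 to 20 weeks (section 4) and food reintroduction of 2 to 8 weeks (section 4). I use 52.18/12 = 4.35 weeks per month, and take Appt 11 as the end of food reintroduction when phases vary. Participants moved out of TDR before week 12 are left aside.

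For a control randomised at month 6:

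- Shortest, 12 + 2 = 14 weeks = 3.2 months: 6 + 3 + 3.2 = month 12.2
- Scheduled, 19 weeks = 4.4 months: 6 + 3 + 4.4 = month 13.4
- Longest, 20 + 8 = 28 weeks = 6.4 months: 6 + 3 + 6.4 = month 15.4
- With the synopsis's 6 months of treatment: 6 + 3 + 6 = month 15

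The number of controls affected, assuming even recruitment, 1:1 allocation (12.5 controls) and strict closure, is:

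| Course | Closure | Latest randomisation | Share of window missed | Controls |
|---|---|---|---|---|
| 14 weeks | month 13 | month 6.8 | 0% | 0 |
| 14 weeks | month 12 | month 5.8 | 3% | 0.4 |
| 19 weeks | month 13 | month 5.6 | 6% | 0.7 |
| 19 weeks | month 12 | month 4.6 | 23% | 2.8 |
| 28 weeks | month 13 | month 3.6 | 40% | 5.1 |
| 28 weeks | month 12 | month 2.6 | 57% | 7.1 |

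The first-column courses exclude the 13-week wait, which is added before the cut-off is found. For 19 weeks this gives (13 + 19)/4.35 = 7.4 months, and 13 − 7.4 = 5.6.

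**The case against.** The best defence is that acceptability does not rest on this questionnaire alone. The synopsis counts engagement, completion and attrition, and section 4.2 makes retention a main outcome. Sections 3.5 and 6 record intolerance and poor compliance, and section 4 records reasons for leaving a phase early. The synopsis also promises written feedback on the programme without tying it to completers, and a psychological process questionnaire that includes satisfaction with outcomes is given through most of the course. A reader might infer that the main question will be answered from completers only, and these provisions show that this goes too far. What stands is narrower. Counts show how many left, and staff records show a reason, but neither is the participant's own view. The psychological questionnaire is not an acceptability scale and stops when attendance stops. The written feedback has no stated timing and no route to leavers.

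A second defence is that the 25% need not be people who disliked the diet. Section 6.1 mentions the pandemic, and nothing forbids asking someone who has discontinued. Both points are fair. They make the direction of the error likely rather than certain, and the zero column in the table is a real possibility.

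A third is that the reporting denominator may be set in the statistical analysis plan that section 6.2 refers to, which is not at hand. That is true of the denominator, but an analysis plan cannot supply answers that were never collected.

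On the timeline, a reader might infer that late-randomised controls never reach Appt 11 and that this too inflates acceptability. The protocol supports neither step. Section 7.0 gives a projected length and does not say that controls still in treatment are dropped. A control cut off by the calendar is lost because of randomisation date, not because of opinion of the diet.

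**Conclusion.** The concern holds for non-completers. As scheduled, the acceptability questionnaire would be answered mainly by completers, about 19 of 25, and the result is likely to be too high by 0 to about 24 percentage points. That range assumes the 25% loss in section 6.1, that non-completers are not asked, and that they are no more favourable than completers. Where the truth lies within it depends on views that the protocol cannot give, so no single value should be quoted.

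The timeline conflict is real but secondary. Six months of recruitment plus the control wait plus the 19-week course does not fit 13 months, and fits the synopsis's 1 year less well. On the scheduled course with closure at month 13, fewer than one control is affected. The number becomes material only with closure at month 12 or with extended phases. It costs numbers and precision, not validity.

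**What to change.** - Give the same short questionnaire to every participant at the end of TDR or at withdrawal, whichever comes first, and again at Appt 11. Use telephone or post where needed; section 4 already allows telephone contact.
- Add the questionnaire as a row in Appendix A, and state in the synopsis and section 4.1 that it is the acceptability measure.
- Report acceptability with all who started TDR as the denominator, and show non-responders openly, for example as best-case and worst-case bounds. With 6 of 25 missing, those bounds are 24 points apart, and each exit form returned narrows them by 4 points (1/25).
- Reconcile the 1 year and 6 months of treatment in the synopsis and the 13 months in section 7.0 with the delayed control pathway, restating the total duration as up to about 15.5 months (6 + 3 + 6.4 = 15.4). Closing randomisation early enough to protect the longest course, at about month 3.6, would give up 40% of the recruitment window in a study that asks whether people can be recruited, so it is not the cheaper choice.

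The cost of the first three items is one extra short form per participant, with some chasing of those who leave. Restating the duration is an edit on paper, though any actual extension needs staff time, which the study team would have to cost.
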